#### 2.3.8 Determination of biomarkers of endothelial damage

At the Salamanca Primary Care Research Unit (APISAL), 6 mL of blood will be extracted in 2 3K-EDTA tubes, then centrifuged (10 min at 2,500 rpm), and the plasma obtained will be frozen at −20°C. Within a maximum period of 1 month, samples will be transferred in specific freezers for biological samples of an infectious nature which will maintain the correct temperature during transport in dry ice, to the Laboratory for Biomedical Research in Respiratory Infection and Sepsis (BioSepsis) at the Faculty of Medicine at the University of Salamanca, where they will be kept at −80°C. In the BioSepsis laboratory, the plasma concentration of the following biomarkers will be measured using ELLA-SimplePlexTM (Biotechne) technology: ICAM-1, VCAM-1, Angiopoietin-2, Endothelin-1, IL-6, IL -15, TNF-alpha, IL-10, PD-L1, CXCL10, IFN-gamma, according to manufacturer’s specifications. ELLA-SimplePlex technology is a microfluidic-based immunoassay which allows biomarkers to be quantified in 25 ul of plasma in a multiplex format, with extremely high reproducibility and in just 90 min. This system uses cartridges pre-loaded with everything necessary for biomarker quantification, including the calibration curve. To perform the assay, the sample will be diluted in the buffer provided, loaded into the cartridge, and introduced into the ELLA-SimplePlex system. The entire process is then automated: the sample and buffer mixture passes through a microfluidic channel which has antibodies binding the protein of interest. The system then washes off any analyte not bound to the antibody and adds the detection reagent. Because each channel has three nanoreactors coated with the capture antibody, the system provides each result in triplicate. The concentrations of each analyte in pg/ml will be obtained from the calibration curve using the system’s software. This technology allows high reproducibility and will permit results obtained in this project to be compared to those already published by our group in patients during the acute phase of SARS-CoV-2 infection (Bermejo-Martin et al., 2020). The laboratory has reference values in healthy people.

#### 2.3.9 Target organ injury

Kidney and heart evaluation: Kidney function will be assessed through the glomerular filtration rate estimated with the equation of the Chronic Kidney Disease Epidemiology Collaboration (CKD-EPI) (Levey et al., 2009) and the albumin-creatinine ratio, following the ESH criteria (Williams et al., 2018b). The heart will be examined by ECG. Left ventricular hypertrophy will be considered for Sokolow-Lyon index >3.5 mV, or Cornell VDP >2440 mV × ms (Williams et al., 2018b).

Retinal vasculature assessement: Nasal and temporal images focused on the optic disc of both eyes, taken with the subject in a sitting position, will be obtained by a qualified researcher using a TOPCON TRC NW 200 non-mydriatic retinograph (Topcon Europe BC, Capelle aan den IJssel, Netherlands). Employing the ALTAIR software (registration number: 00/2015/995), specifically developed by our research group, we will measure the thickness of the arteries, the thickness of the veins, and the artery/vein index; the area and length of the retina will be calculated semiautomatically (Maderuelo-Fernandez et al., 2020)

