### 2.2 Study population

Through consecutive sampling, we will select 300 subjects who meet the clinical definition of persistent COVID of the WHO, established by international Delphi consensus, along with patients, their representatives, and experts from the five continents. Persistent COVID is the condition that occurs in individuals with a history of probable or confirmed SARS-CoV-2 infection, generally three months after the onset of the disease, with symptoms that last for at least two months and cannot be explained by an alternative diagnosis. The common symptoms include, among others, fatigue, difficulty in breathing and cognitive dysfunction, and they generally have an impact on daily functioning. They can be de novo after the initial recovery from an acute episode of COVID-19 or persist from the initial disease, and they can also fluctuate or relapse over time (Soriano et al., 2022). The exclusion criteria of the study will be: terminal subjects, subjects who cannot go to the health centres, subjects with a history of cardiovascular disease (ischemic heart disease or cerebrovascular disease) and glomerular filtration rate below 30%. The individuals will be recruited from the registries of the Primary Care offices and the Persistent COVID Office of Internal Medicine in the health area of Salamanca. The sample size was calculated using the GRANMO free software (http://www.imim.cat/ofertadeserveis/software-public/granmo/), detecting a difference in cf-PWV of 0.35 metres/second between subjects with persistent COVID and a sample of Spanish population without cardiovascular disease (Gómez-Sánchez et al., 2020a). Accepting an alpha risk of 0.05 and a beta risk below 0.2 in a bilateral contrast, and assuming a standard deviation of 2.1, a total of 283 individuals are required to detect the indicated difference as significant. Therefore, the 300 subjects that will be included in the study will be sufficient. The subjects included in the study are shown in Figure 1. The patients did not participate in the design of the study; however, they will participate actively in the recruitment, by disseminating the objectives of the study and the inclusion criteria through their organisations. By means of discussion groups, we will investigate the opinions and experiences of the study population about the influence of persistent COVID on vascular health. Similarly, their opinions and attitudes will be considered to facilitate the transfer to the clinical practice. At the end of the study, we will send a detailed report to each patient with the results of the tests conducted. Moreover, a dissemination session will be organised for all the patients included in the study.

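### The Cornell product cut-off for left ventricular hypertrophy pairs a number and a unit that do not fit: 2440 in mV × ms appears ten-fold too high

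*Protocol article*

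**What the plan says.** Section 2.3.9 (Target organ injury) states the method for the heart, "The heart will be examined by ECG", and then the decision rule: "Left ventricular hypertrophy will be considered for Sokolow-Lyon index >3.5 mV, or Cornell VDP >2440 mV × ms". The two limits are joined by *or*, so meeting either one is enough. A guideline is cited for the rule.

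The article gives no other unit for the Cornell product, no formula for it, no conversion and no QRS duration. Table 1 names the ECG machine as the instrument for the heart and adds nothing on how the product is obtained. The Methods part of the abstract lists the heart among the organs to be examined for injury. Hypertrophy is the only heart finding for which the article gives a definition.

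**The concern.** Both limits in the sentence are meant to mark the same condition, yet they sit on very different scales. The first is a voltage of 3.5 mV. The second is a product that, divided by any ordinary QRS duration, implies a voltage several times larger. That pattern suggests a number belonging to one unit printed with another.

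At stake is one of the two routes to a positive classification for a target-organ variable. A threshold out of reach in its stated unit is silent when coded: it raises no error and produces only negatives on that arm. Anyone positive on Cornell but not on Sokolow-Lyon would then be recorded as free of hypertrophy.

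**Working it through.** **Inputs from the protocol article, section 2.3.9**
- Cornell limit: "Cornell VDP >2440 mV × ms".
- Voltage scale for comparison: "Left ventricular hypertrophy will be considered for Sokolow-Lyon index >3.5 mV".

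**Assumptions, not in the article**
- QRS duration of 80 to 200 ms. The upper end is deliberately wide.
- ECG calibration of 10 mm = 1 mV.

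The article derives no figure here that could be reproduced. The check is one of units.

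**Step 1. Voltage needed under the printed unit.** Product = voltage × QRS duration, so voltage needed = 2440 / QRS duration.

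**Step 2. Voltage needed if 2440 is in mm × ms.** 2440 mm × ms ÷ 10 mm per mV = 244 mV × ms, so voltage needed = 244 / QRS duration.

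| QRS (ms) | 2440 mV × ms: voltage needed (mV) | Ratio to 3.5 mV | 244 mV × ms: voltage needed (mV) | Ratio to 3.5 mV |
|---|---|---|---|---|
| 80 | 30.5 | 8.7 | 3.05 | 0.87 |
| 100 | 24.4 | 7.0 | 2.44 | 0.70 |
| 120 | 20.3 | 5.8 | 2.03 | 0.58 |
| 150 | 16.3 | 4.6 | 1.63 | 0.46 |
| 200 | 12.2 | 3.5 | 1.22 | 0.35 |

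Sokolow-Lyon and Cornell are different indices, so the ratios compare orders of magnitude only. They are not an equivalence.

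**Step 3. The same check from the other side.** QRS duration needed = 2440 / voltage.
- At 3.5 mV: 2440 / 3.5 = 697 ms.
- At an extreme 7 mV: 2440 / 7 = 349 ms.

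**Step 4. An extreme case.** A very large voltage with a very wide QRS, 7 mV × 200 ms, gives 1400 mV × ms. That is 1400 / 2440 = 57% of the printed limit.

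The conclusion does not hinge on where in the assumed range the QRS falls. The printed limit stays out of reach throughout, while a limit one tenth as large lies on the scale of the neighbouring criterion.

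**The case against.** The strongest reply is that a wrong label in the text is not a misclassified participant. The article does not say who or what computes the product, or in which unit it is recorded. If the ECG machine or the reader works in mm × ms, the figure 2440 does its job and only the printed unit is wrong. This stands, and it makes any under-counting conditional on literal use of the rule with values in mV × ms.

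Three further inferences are tempting, and the article does not support them:
- *The hypertrophy definition as a whole fails.* It does not. The *or* leaves Sokolow-Lyon operating, and only the Cornell arm is disabled on a literal reading.
- *Prevalence will not be comparable with other populations.* The external comparisons planned in sections 2.1 and 2.4 concern vascular structure, vascular function, vascular ageing and standardised arterial stiffness. No external comparison of hypertrophy is described.
- *The error is built into the database.* Section 2.4 says that data are entered in REDCap through a project questionnaire. It describes no derived hypertrophy variable.

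It can also be said that the QRS range and the calibration come from outside the article. That is true, and they are labelled as assumptions above. The QRS range would have to be wrong by a large margin to change the result. The cited guideline is not available here, so the view that 2440 goes with mm × ms is an inference from scale, not a check against the source.

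Finally, the weight in the study is limited. Hypertrophy is not named in the main or secondary objectives at the end of the Introduction.

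**Conclusion.** The point holds as a wrong threshold in the written definition. Number and unit do not belong together, and under the calibration assumption the printed limit appears to be ten times too high. Over an assumed QRS of 80 to 200 ms, no plausible ECG voltage would meet it.

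The consequence is conditional. Applied literally to values in mV × ms, the Cornell arm classifies no one and the variable reduces to Sokolow-Lyon. The number of participants positive on Cornell alone is not given and cannot be derived, so the size of any under-count is unknown.

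A reader might infer that the main results are at risk. They are not:
- The sample-size statement in section 2.2, "a total of 283 individuals are required to detect the indicated difference as significant", rests on cfPWV with a difference of 0.35 m/s and a standard deviation of 2.1.
- The vascular-ageing classes in section 2.3.7 use carotid injury, peripheral arteriopathy and percentiles of cfPWV or baPWV, not ECG hypertrophy.

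This is a correction that should be made because it concerns a stated decision limit and costs almost nothing.

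**What to change.** Check the Cornell limit in section 2.3.9 against the guideline cited there and make number and unit agree. At 10 mm = 1 mV, the two internally consistent pairings are 2440 with mm × ms and 244 with mV × ms. The source should settle which is printed.

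Before participants are classified, confirm the unit in which the Cornell product is recorded, whether by the ECG machine or by hand, and confirm that it matches the threshold used. If any participants have already been classified with mismatched units, reapply the rule to the stored values.

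The cost is one number or unit in the text and one check of the recorded variable. No sample-size or design change follows.

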#### 2.3.10 Psychological factors and cognitive alteration

The symptoms of anxiety and depression will be evaluated using the Spanish version (Monton et al., 1993) of Goldberg’s Anxiety and Depression Scale (GADS) (Goldberg and Hillier, 1979), which contains a subscale of anxiety (questions 1–9) and a subscale of depression (questions 10–18). The cut-off point is 4 or higher for the anxiety subscale and 2 or higher for the depression subscale. Cognitive function will be evaluated using the Montreal Cognitive Assessment (MoCA) scale (Nasreddine et al., 2005), which is a tool designed for the evaluation of cognitive performance that has been validated in Spain (Lozano et al., 2009). The MoCA assesses the following cognitive domains: attention and concentration, executive functions, memory, language, visuoconstruction abilities, conceptual thinking, calculation and orientation. The maximum score is 30 points, with a score of 26 or higher indicating normal cognitive performance.

#### 2.3.11 Analytical tests

Venous blood samples and urine samples will be collected, between 8 a.m. and 9 a.m., with the participants fasting and avoiding smoking or consuming alcohol or caffeine for 12 h. At the time of inclusion, At the time of inclusion, an analysis will be carried out to determine basal glycemia, urea, uric acid, creatinine, glomerular filtration rate estimated with the CKD-EPI equation, ionogram including calcium, thyroid function, lipid profile, complete blood count measuring (leukocytes, lymphocytes, neutrophils, and eosinophils) iron, ferritin, folic acid, liver profile including Gamma-GT, fibrinogen, haptoglobin, D-dimer, ESR, PCR, and albumin and urine albumin-creatinine ratio. We will also gather, if they exist, the analytical data during the acute episodes. The samples will be collected in the San Juan health centre, where the APISAL research unit is located; then, they will be sent by preferred internal circuit to the Clinical Analyses Service of the University Assistance Complex of Salamanca in collaboration with the Biochemistry and Immunochemistry Unit of CAUSA. The samples will be coded and the analytical techniques used will be those standardised by the laboratory.

### 2.4 Statistical analysis

The data will be registered using the REDCap platform (Research Electronic Data Capture) (Harris et al., 2009; Harris et al., 2019) with a data-gathering questionnaire designed for the project. The normal distribution of the variables will be verified through the Kolmogorov-Smirnov test. The arterial stiffness variables will be standardized and expressed as Z scores to compare results with other reference populations. The analysis of the difference of means between variables of two categories will be performed through Student’s t-test or Mann-Whitney U-test, depending on each case, whereas the qualitative variables will be analysed through X^2^ test. To analyse the relationship between qualitative variables of more than two categories and quantitative variables, an analysis of variance (ANOVA) will be conducted, and a Bonferroni’s test will be performed for the post hoc analyses. The Kruskal-Wallis test will be applied in those cases in which the variables do not show a normal distribution. The analysis of covariance (ANCOVA) will be carried out to control for the variables that can be affected by the results as confounding factors. The relationship among quantitative variables will be analysed using Pearson’s or Spearman’s correlation, depending on each case. In the multivariate analysis, we will use multiple linear regression and logistic regression analyses, with the necessary adjustments according to the type of variables analysed. All variables will be analysed disaggregated by sex, and, whenever applicable, the differences will be analysed from a gender perspective, considering the known influence of gender on many pathologies, particularly cardiovascular and cerebrovascular diseases. The data will be analysed using the SPSS v28.0 statistical package for Windows (IBM, Armonk, New York: IBM Corp). Statistical significance will be set at p < 0.05.

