#### 2.3.7 Vascular ageing

Vascular ageing will be evaluated with cfPWV, baPWV or vascular age estimated using a VaSera VS-2000 device (Fukuda Denshi Co, Ltd, Tokyo, Japan) as measures of arterial stiffness. Firstly, the subjects who present vascular injury (injury in the carotid artery or peripheral arteriopathy) will be classified as EVA. Secondly, the subjects will be classified as EVA, NVA and HVA if the values of cfPWV or baPWV are above percentile p90, between p10 and p90, and below p10, respectively. (Gomez-Sanchez et al., 2020)

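### Section 2.4 fixes equal-variance ANOVA with Bonferroni and leaves it only for non-normality, although the vascular-ageing factor has small outer classes; if class variances differ, the 5% level is not delivered

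*Protocol article*

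**What the plan says.** Section 2.4 (Statistical analysis) assigns methods by type of variable. For a factor with more than two categories and a quantitative outcome, "an analysis of variance (ANOVA) will be conducted", followed by Bonferroni post hoc tests. The only assumption check named is Kolmogorov-Smirnov for normality, and the only stated reason to leave ANOVA is non-normality, in which case Kruskal-Wallis is used. Unequal variance is not mentioned. The threshold is explicit: "Statistical significance will be set at p < 0.05". Everything is also to be analysed separately by sex.

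Section 2.3.7 (Vascular ageing) defines a three-class factor. First, "the subjects who present vascular injury (injury in the carotid artery or peripheral arteriopathy) will be classified as EVA". The remaining subjects are then placed in early (EVA), normal (NVA) or healthy (HVA) vascular ageing according to whether cfPWV or baPWV is "above percentile p90, between p10 and p90, and below p10, respectively". The section does not name the population that supplies the percentiles. The Introduction favours the study's own population, while section 2.1 uses an external reference group to judge whether vascular ageing is altered.

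Section 2.2 sets the size: "Through consecutive sampling, we will select 300 subjects".

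**The concern.** Classical ANOVA and Bonferroni tests on the pooled error both estimate a single common variance. When group sizes are similar, a wrong common variance does little harm. When one group holds most of the subjects, the pooled variance is close to that group's variance, and the standard error for a small group is wrong whenever that group's spread differs.

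The vascular-ageing factor has this shape by construction. Its classes also have no particular reason to share a variance: EVA combines subjects with carotid or peripheral injury and subjects with high pulse wave velocity. The second main objective in the Introduction relates symptoms, lifestyles and psychological, cognitive and inflammatory factors to vascular ageing, among other vascular measures. Comparing a quantitative factor across the three classes would fall under the ANOVA rule. At stake is whether a p-value below 0.05 in those comparisons means what the plan says it means.

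**Working it through.** **Inputs from the article.** N = 300 (2.2); cut-offs p10 and p90 and the injury rule (2.3.7); nominal level 0.05, ANOVA and Bonferroni (2.4).

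**Assumptions.** No SD is given by class. The NVA SD is set to 1 and the outer SDs are varied from 0.67 to 2. Data are normal and the class means are equal, so every rejection is a false positive.

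**The plan's own figure.** Section 2.2 plans on "detecting a difference in cf-PWV of 0.35 metres/second", "assuming a standard deviation of 2.1", with "Accepting an alpha risk of 0.05 and a beta risk below 0.2 in a bilateral contrast". The one-sample formula gives n = ((1.960 + 0.842) × 2.1 / 0.35)² = 282.56, rounded up to 283. This is the stated figure. It does not involve the vascular-ageing classes, so nothing below affects it.

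**Class sizes.** 0.10 × 300 = 30, 0.80 × 300 = 240, 0.10 × 300 = 30.

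**The mechanism by hand.** Take SDs 1 / 1 / 1.5 for HVA / NVA / EVA.
- Pooled variance: (29 × 1 + 239 × 1 + 29 × 2.25) / 297 = 1.122.
- Variance of the EVA-NVA mean difference as the pooled test sees it: 1.122 × (1/30 + 1/240) = 0.0421.
- True variance of that difference: 2.25/30 + 1/240 = 0.0792.
- The standard error is too small by a factor of √(0.0792 / 0.0421) = 1.37.
- The Bonferroni critical value for three comparisons (0.05/3 = 1.7% each, 297 df) is 2.41. It acts like 2.41 / 1.37 = 1.76, a two-sided error of about 8% instead of 1.7%. Simulation gives 8.2%.

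**Overall ANOVA at 30/240/30** (simulated, 100,000 data sets per setting):

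| Outer-class SDs relative to NVA | ANOVA error |
|---|---|
| Equal | 4.9% |
| One outer class at 1.25 / 1.5 / 2 | 8.1% / 11.8% / 18.6% |
| Both outer classes at 1.25 / 1.5 | 10.9% / 17.3% |
| Both outer classes at 0.8 / 0.67 | 1.7% / 0.5% |

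The Bonferroni family-wise error with one outer class wider is 7.1% / 10.6% / 17.5%. Sizes 15/120/15, which is each sex if the sexes split equally (an assumption), give almost the same figures.

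**If the shares are not 10/80/10**, with only EVA wider, at 1.25 / 1.5:
- EVA at 20% (30/210/60): 6.7% / 8.8%.
- EVA at 25% (15/210/75): 6.2% / 7.2%.

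At 15/210/75 with both outer classes wider, the error is again larger: 9.5% / 13.5%.

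**The plan's fallback.** Kruskal-Wallis at 30/240/30 with both outer classes at 1.25 / 1.5 / 2 gives 7.7% / 10.5% / 15.1% (4,000 data sets each), so it does not protect against unequal spread either.

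**Welch's ANOVA** stays between 4.8% and 5.2% in all these settings. With equal SDs, its power falls from 79.1% to 77.1% (class means -0.4 / 0 / 0.4 SD), or from 44.3% to 41.9% (EVA alone shifted by 0.4 SD).

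**The case against.** **Direction is not known.** A reader might infer that the plan raises the false-positive rate to 8-19%. The article does not support that. It gives one SD (2.1, for cfPWV) and none by class. Inflation needs a small class to be the more variable one; otherwise the test is conservative. The 19% end needs twice the SD, a fourfold variance, which is not a modest difference. This objection stands, and the claim is conditional for that reason.

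**The 10/80/10 split is nominal.** The injury rule takes effect first and can enlarge EVA, and the percentile source is not fixed in 2.3.7. This stands too. It weakens the inflation when EVA is the wider class, but does not remove it.

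**Student's t-test.** It is tempting to extend the point to two-group comparisons. Section 2.4 gives the t-test to two-category variables, offers Mann-Whitney beside it, and fixes no group sizes; with 150 against 150 the pooled t-test stays at about 5%. The documents do not show that a change is needed there. Nor do they show a need for robust standard errors in ANCOVA or regression, for which no calculation was made.

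**Role of the comparison.** The article does not say that ANOVA across these classes is the test for a main objective. Correlation and regression are also named, and the study is descriptive. This limits the weight of the point.

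**Skewed data.** Welch's test can itself fail when small classes are skewed. With identical lognormal distributions (log-SD 0.5 and 1.0) at 30/240/30 it gave 6.6% and 11.2%, against 5.2% and 5.0% for ANOVA. This is largely answered by the plan's own rule: at n = 300 a normality test almost always flags strong skew and sends the variable to Kruskal-Wallis. Under mild gamma skew, Welch stayed at 5.2-6.5%.

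**Level of detail.** Variance checks are often left to an analysis plan, which is not shown here. But the article does more than stay silent: it states both the default test and the condition for leaving it, and that condition omits the assumption most exposed by these class sizes.

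**Conclusion.** The point holds in conditional form. Section 2.4 commits to a pooled-variance test and names only non-normality as a reason to depart from it, while 2.3.7 creates a factor with small outer classes. If class variances differ, the nominal 5% is missed in one direction or the other: about 8-12% with one outer class at 1.25-1.5 times the SD, about 11-17% with both, and about 0.5-2% when both outer classes are less variable. With EVA at 20-25% and only EVA wider, the figure is about 6-9% at 1.25-1.5 times.

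All of this rests on assumed class SDs, normal data and nominal class shares. It concerns comparisons across the vascular-ageing classes only. It is a cheap improvement to the stated method and does not invalidate the study.

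**What to change.** In section 2.4, for comparisons across EVA, NVA and HVA in variables that pass the normality check, replace ANOVA with Welch's ANOVA and the Bonferroni post hoc tests with Games-Howell. Make this the default, without a preliminary test of equal variances. Both are available in SPSS, which the study already uses.

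The cost is a change of wording and about 2 points of power if the variances turn out equal. No data collection changes, and the 283 stays as it is. Welch's t-test for two-category variables and robust standard errors in the models are optional additions.

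### Holm's step-down adjustment could replace Bonferroni for the post hoc pairs at the same family-wise error; the power gained is never negative but depends on class sizes and effects the protocol does not give

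*Protocol article*

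**What the plan says.** Section 2.4 (Statistical analysis) sets the route for a quantitative variable across a factor with several categories: "To analyse the relationship between qualitative variables of more than two categories and quantitative variables, an analysis of variance (ANOVA) will be conducted", after which "Bonferroni’s test will be performed for the post hoc analyses". Kruskal-Wallis replaces ANOVA when normality fails; no separate pairwise method is named for that case. The general criterion is "Statistical significance will be set at p < 0.05".

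Several factors in the protocol have three or more ordered categories. Vascular ageing (section 2.3.7) is classed as EVA, NVA or HVA according to whether cfPWV or baPWV lies "above percentile p90, between p10 and p90, and below p10, respectively". CAVI (2.3.6), the malnutrition and frailty scales (2.3.3) each have three classes, and alcohol consumption (2.3.4.3) has four. Section 2.4 also has every variable analysed separately by sex, which makes the classes smaller.

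The only comparison with a stated power is in section 2.2: cfPWV in persistent COVID against a reference population. No power, class size or class difference is given for any post hoc pair.

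**The concern.** Bonferroni judges each of m pairs at 0.05/m whatever the other pairs show: 0.0167 with three classes (m = 3) and 0.0083 with four (m = 6). Holm orders the same p-values and tests the smallest at 0.05/m, the next at 0.05/(m − 1), and so on, stopping at the first failure. With three classes the thresholds are 0.0167, 0.025 and 0.05. Holm controls the family-wise error strongly under the same conditions as Bonferroni, so for significance decisions alone the protocol fixes a method that another method never does worse than.

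What is at stake is how completely a graded pattern is described. When the means rise across ordered classes, the contrast of the two extremes usually reaches significance first, and the adjacent contrasts (EVA against NVA, HVA against NVA) are those Bonferroni tends to miss. This touches the second main objective, which relates symptoms, lifestyle and psychological, cognitive and inflammatory factors to vascular ageing and to the endothelial biomarkers, wherever a categorical factor is used.

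**Working it through.** **The plan's own figure.** Section 2.2 gives "Accepting an alpha risk of 0.05 and a beta risk below 0.2 in a bilateral contrast", "detecting a difference in cf-PWV of 0.35 metres/second between subjects with persistent COVID and a sample of Spanish population" and "assuming a standard deviation of 2.1", with 283 required. For one sample against a fixed reference mean:

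n = [SD × (z0.975 + z0.80) / difference]² = [2.1 × (1.960 + 0.842) / 0.35]² = 282.6, rounded up to 283.

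The stated size reproduces. It contains no between-class contrast, so the choice of post hoc method does not enter it. The standardised difference is 0.35/2.1 = 0.167 SD.

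**Inputs for the post hoc pairs.** Total N = 300 and alpha 0.05 come from sections 2.2 and 2.4. The following are assumptions:
- Class sizes. 30/240/30 would follow from p10/p90 cuts taken within the study sample (0.10 × 300 = 30), if the rule in 2.3.7 that first assigns patients with vascular injury to EVA moved nobody. 100/100/100 and 75 × 4 are shown as alternatives.
- Normal data with equal variances.
- Class means, as in the tables, in SD units.

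**Method.** 100,000 simulated data sets per setting, pooled-variance t-tests for all pairs. Bonferroni rejects if p ≤ 0.05/m; Holm is applied to the same p-values. Requiring a significant ANOVA first for both methods changes the per-pair powers by less than about 1 point.

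**Three classes, means 0, d, 2d: power for one adjacent pair, Bonferroni → Holm**

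| d (SD) | 30/240/30 | 100/100/100 |
|---|---|---|
| 0.167 | 6% → 7% | 11.0% → 13.6% |
| 0.3 | 20% → 25% | 38.9% → 49.9% |
| 0.4 | 36.7% → 46.7% | 66.4% → 79.3% |
| 0.5 | 57.2% → 69.3% | 86.9% → 94.1% |
| 0.6 | 75.3% → 85.7% | 96.6% → 98.8% |

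The gain runs from about 1 point to about 13 (79.3 − 66.4 = 12.9). With 30/240/30 and d = 0.4, the chance of declaring all three true differences rises from 12% to 26%.

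**Four classes of 75, equally spaced means: gain for an adjacent pair**

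| d (SD) | Gain |
|---|---|
| 0.2 | about 3 points |
| 0.3 | about 10 points (21% → 31%) |
| 0.4 | 18 to 19 points |
| 0.5 | 18 to 19 points |

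**Three classes, only one outer class shifted (means 0, 0, d).** With 30/240/30, the truly different adjacent pair goes from 37.0% to 38.2% at d = 0.4 and from 56.9% to 58.2% at d = 0.5. With equal classes the gain is at most about 3 points. The contrast of the two outer classes gains somewhat more, up to about 5 points (47.1% to 52.1% with 30/240/30 at d = 0.6).

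**What does not change.** The chance of at least one rejection is the same under both methods in every setting (78.9% for each at 30/240/30, d = 0.4), because the first Holm step is the Bonferroni test of the smallest p-value. With no true differences, both reject at least once in 4.1% to 4.4% of runs.

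**The case against.** The strongest reply is that nothing here is wrong. Bonferroni after ANOVA is standard and valid, and these are unpowered comparisons in a descriptive study that also plans ANCOVA and regression. That stands: this is an efficiency gain and not a correction.

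A reader might infer from the 30/240/30 example that the plan loses a fixed 10 points or so on adjacent contrasts. The documents do not support that. They give no class differences, and equally spaced means are the pattern that favours Holm. The class sizes are also uncertain. The injury rule in 2.3.7 can enlarge EVA, and the source of the percentiles is open: the Introduction favours those of the study population, whereas section 2.1 judges vascular ageing against an external reference group. Nor is 0.167 SD a benchmark for the classes, since it is a difference from a reference population. Only a range can be defended.

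A reader might also infer that Bonferroni gives up power for nothing. It does offer something: simultaneous confidence intervals that match its tests directly, which step-down Holm does not provide simply. Section 2.4 mentions no such intervals and works with a p-value criterion, so this drawback of Holm is small but real.

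Finally, with exactly three classes, unadjusted pairwise tests after a significant ANOVA also control the family-wise error and beat Holm (about 52% against 47% at 30/240/30, 0.4 SD). That is correct, but the property does not carry over to four or more classes, which the protocol also has. Holm improves on Bonferroni, or equals it, for any number of classes.

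**Conclusion.** The point holds as a low-severity improvement. It is certain that Holm keeps the same strong family-wise error and is never less powerful than the Bonferroni test fixed in section 2.4. The size is conditional on assumed normal data with equal variances, N = 300 and assumed class sizes and means. For an adjacent contrast it is about 1 to 13 points with three equally spaced classes, up to about 19 with four, and at most about 3 if only one outer class differs. The protocol cannot narrow this range. The benefit lies in how many of the true differences are found once one pair is already significant. The sample size and the cfPWV comparison against the reference population are unaffected.

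**What to change.** In section 2.4, replace Bonferroni's test by Holm-adjusted pairwise p-values for the post hoc comparisons, and state that the same adjustment applies to the pairwise tests after Kruskal-Wallis. The cost is a few words and a simple reordering of p-values that the analysis produces anyway; no new data or assumption is needed. If simultaneous confidence intervals for the pairwise differences are reported, give the Bonferroni intervals alongside the Holm p-values and say so, because a pair may be significant by Holm while its Bonferroni interval still includes zero.
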